### Trial Arms:

**Phase I:**

*Arm 1: Non-intervention arm:*

The non-intervention arm will be based on the existing clinical diagnosis, pre-referral treatment and referral to a clinic in areas where RDTs have not been deployed at CHW level. Arm 1 CHWs will receive refresher training according to the National Strategy for CBMM which includes the current IMCI guidelines.

Vs:

*Arm 2: RDT Arm*

Provision of community level diagnostics by rolling out RDTs to CHWs through the national strategy for Community based Management of Malaria. The arm has been designed exactly as the current National guidelines for RDT implementation..The arm will include:

- Clinic level microscopy or RDT and CHWs using RDTs to provide parasitological diagnosis to diagnose, treat and/or refer patients. Under this scheme, CHWs will be provided with CQ, SP and artesunate (AS). Depending on the diagnostic result, they prescribe according to the National Treatment Guidelines (CQ for confirmed vivax, SP and AS for confirmed falciparum, and no antimalarial for a negative result).
- CHW training will be conducted exactly as described in the CBMM strategy, using a “trickle down approach” where Training of Trainers takes place at the central level for provincial trainers of local NGOS who run the health service. These, in turn, run workshops for training CHSs and CHWs (see section 2.2 for pre-evaluation of training and roll-out). Participants will receive training to enforce revised IMCI guidelines, taken from the CBMM strategy document, which include an RDT in the algorithm for fever (see annex 2).
- There are no plans for additional support or refresher training, and no plans for quality control and assurance contained in the National Plan.
- CHWs are not equipped with suitable storage facilities for the RDTs, for example evaporative coolers.
- Monitoring and evaluation takes place according to the draft strategy.

The second phase of the trial will be initiated in Feb 2012. The second phase of the trial will re-randomise clinics to either the RDT arm (as in arm 2, above) and a third arm (arm 3). The third arm will answer the question: “how can the performance of RDTs at community level be enhanced?”. The same set of outcomes will be used to measure the relative effectiveness of each approach. A revised random allocation using the same methods will be conducted for the Phase II randomisation.

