### Randomisation Methods:

### Number of unrestricted allocations

The study is a stratified cluster randomised trial with a total of 22 clusters.

In Kunduz the total number of ways of allocating the 10 clusters to the two intervention groups, assuming equal number of clusters per arm:

$$\binom{10}{5}\binom{5}{5}=252$$

In Nangahar the total number of ways of allocating the 12 clusters to the two intervention groups, assuming equal number of clusters per arm

$$\binom{12}{6}\binom{6}{6}=924$$

Therefore in total there are: 252 x 924 = 232,848 possible allocations of 22 clusters into the 2 study arms after stratification.

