### Trial Secondary Outcomes:

- % of Pf cases treated with ACT.
- % of patients <10 years of age who are correctly treated (estimated at 40% of all patients)
- % of malaria negative patients receiving antimalarial drug
- % of malaria negative patients receiving antibiotics
- % of patients treated per policy

Per policy defined as:

- Suspected malaria which is PCR confirmed treated with CQ/SP
- Community based diagnosed Pf, subsequently confirmed as Pf treated with SP/AS
- Community based diagnosed Pv, subsequently confirmed as Pv treated with CQ
- No antimalarial given to negative cases (confirmed by PCR)
- Proportion of patients incorrectly treated in each arm, including data collected at the clinic level.
- Time to first treatment from onset of symptoms.
- Cost per patient correctly treated.
- Cost per patient treated per policy.
- Invalid rate, specificity and sensitivity of RDTs deployed at community level (against PCR).
- Number of patients attended by CHWs and type of attendance.
- Number and proportion of patients successfully referred by CHWs to BHCs.
- Proportion of malaria negative and positive given antibiotics at CHW and/or clinic level.

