### Statistical Methods:

An analysis plan will be developed by the investigators uring the trial. This will be reviewed by the statistician and DSMB prior to use. Broadly, primary and secondary outcomes will be assessed for differences by intervention arm using proportions with appropriate measures of statistical significance, for example chi^2^ test or Fisher’s exact test. Multivariate analysis will be conducted using a variety of potential explanatory variables related to the prescriber and the patients. These parameters are:

- Prescriber variables: Training history (prior to the intervention), age, gender.
- Patient variables: Age, gender, severity of symptoms, range of symptoms.
- Health system variables: clinic type, place of diagnosis and treatment (CHW or clinic).

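### Place of diagnosis and treatment is listed as a covariate without limit; in an arm-effect model on outcomes pooling CHW and clinic data, the estimate would no longer be the total intervention effect

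*Protocol*

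**What the plan says.** Section 2.8.4 (Statistical Methods) has two parts. The comparison of arms comes first: "primary and secondary outcomes will be assessed for differences by intervention arm using proportions with appropriate measures of statistical significance", with chi-square and Fisher's exact tests as examples. A second analysis follows: "Multivariate analysis will be conducted using a variety of potential explanatory variables related to the prescriber and the patients". Its list of variables ends with "Health system variables: clinic type, place of diagnosis and treatment (CHW or clinic". Another entry carries a time limit, "Prescriber variables: Training history (prior to the intervention), age, gender", but place of care carries none, and no outcome is excluded from the multivariate analysis.

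Section 2.5.1 (Trial Arms) describes different pathways in Phase I. Arm 1 rests on "existing clinical diagnosis, pre-referral treatment and referral to a clinic in areas where RDTs have not been deployed at CHW level". Arm 2 has "CHWs using RDTs to provide parasitological diagnosis to diagnose, treat and/or refer patients".

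Section 2.6.1 limits the primary outcome to treatment by CHWs. Section 2.6.2 includes a pooled secondary outcome, "Proportion of patients incorrectly treated in each arm, including data collected at the clinic level", and another on antibiotics given at either level. It also counts successful referral from CHW to clinic as an outcome. Section 2.5.4 states: "The study is a stratified cluster randomised trial with a total of 22 clusters"; the allocations are enumerated separately within Kunduz and Nangahar.

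**The concern.** A covariate in a model that estimates a randomised effect should not itself be open to influence by the allocation. Place of care is open to it. Section 2.7.1 has the CHW choose a diagnosis and a course of action during the consultation, after which the patient may attend the clinic. By then the clinic's arm has long been fixed. Whether the CHW holds a rapid test can change who is treated on the spot and who moves on.

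Conditioning on place compares arms within CHW-treated and within clinic-treated patients. Any part of the effect that works by shifting patients between the two levels is then removed or distorted. At stake is the interpretation of secondary outcomes that combine both levels: an adjusted figure could be read as the effect of deploying the tests when it answers a narrower question.

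**Working it through.** No figure in the protocol is at issue, so there is none to reproduce. Two checks apply.

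**1. Is place fixed before allocation?** No. Clinics are allocated first (2.5.4 and 2.5.5); the CHW decides what to do at each consultation (2.7.1); the pathways differ between Arms 1 and 2 (2.5.1); and referral is measured as an outcome (2.6.2). In Phase II, Arms 2 and 3 share the same pathway wording, so the contrast in stated pathway belongs to Phase I. Place is still settled after allocation in both phases.

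**2. What would adjustment do to a pooled outcome?** This is an illustration on the risk-difference scale, for correct treatment. Incorrect treatment is the complement, so the size is the same and the sign reverses.

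Inputs:
- Correct treatment at CHW level: 10% in Arm 1 and 50% in Arm 2 (section 2.8.1). These are planning values; the protocol notes that they come from clinic data and that no regional CHW estimates exist.
- Correct treatment at clinic level, c: **assumed** equal in both arms, from 30% to 90%.
- Share of patients whose outcome comes from the clinic, q1 in Arm 1 and q2 in Arm 2: **assumed**.
- Arms of equal size.

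Total effect = [(1 - q2) × 0.50 + q2 × c] - [(1 - q1) × 0.10 + q1 × c].

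In a linear model with arm and place, the arm coefficient is a weighted mean of the within-place differences, here 0.40 at CHW level and 0 at the clinic. The weights are
- CHW: (1 - q1)(1 - q2) / [(1 - q1) + (1 - q2)]
- clinic: q1 × q2 / (q1 + q2)

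Worked case, q1 = 60%, q2 = 20%, c = 50%:
- Total: 0.50 - (0.40 × 0.10 + 0.60 × 0.50) = 0.50 - 0.34 = 0.160.
- Weights: 0.4 × 0.8 / 1.2 = 0.2667 and 0.6 × 0.2 / 0.8 = 0.150.
- Adjusted: 0.40 × 0.2667 / 0.4167 = 0.256.
- Shift: +0.096.

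| Clinic share, Arm 1 / Arm 2 | Place-adjusted | Total, c = 30% | c = 50% | c = 70% | c = 90% |
|---|---|---|---|---|---|
| 30% / 30% | 0.280 | 0.280 | 0.280 | 0.280 | 0.280 |
| 40% / 20% | 0.288 | 0.280 | 0.240 | 0.200 | 0.160 |
| 60% / 20% | 0.256 | 0.240 | 0.160 | 0.080 | 0.000 |
| 20% / 40% | 0.288 | 0.280 | 0.320 | 0.360 | 0.400 |

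The adjusted value does not depend on c, because the clinic-level difference is set to zero. Adjusted minus total runs from 0.288 - 0.400 = -0.112 to 0.256 - 0.000 = +0.256. Equal shares give no shift.

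For a CHW-only outcome, place takes one value and drops out of the model, so there is no shift.

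**The case against.** The strongest reply is that section 2.8.4 does not specify an adjusted arm effect at all. The stated comparison of arms is an unadjusted one of proportions. The multivariate sentence follows separately, calls its variables potential, and can be read as a model of what determines correct treatment, where place of care is a legitimate explanatory variable. Detail is deferred to an analysis plan. This stands, and it makes the point conditional. It does not remove the point: the list is affirmative, a later plan would naturally take it over, and nothing confines place to a determinants model.

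Three stronger readings are tempting, and the documents do not support them.

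- *A reader might infer that the trial's main result is biased.* The primary outcome covers treatment by CHWs only, so place cannot distort it.
- *A reader might infer that adjustment inflates the benefit of testing, because Arm 1 refers patients and Arm 2 treats them.* The direction is not given. Arm 1 includes pre-referral treatment, Arm 2 CHWs may also refer, section 2.10.3 has Pf-positive patients referred to a clinic, and section 2.5.7 also enrols clinic patients who never saw a CHW. The last row of the table shows the shift with the opposite sign.
- *A reader might take a 50% clinic correct-treatment rate from section 1.2.* That section says that about half of malaria-negative patients are still given antimalarials after parasitological diagnosis. It gives no overall correct-treatment rate and none by arm of this trial, so the clinic rate is an assumption.

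On province, adjustment for the stratum is commonly left to an analysis plan, so its absence here is not a separate fault, and no figure in the protocol supports a claim of lost precision.

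**Conclusion.** The point holds in conditional form. The protocol lists a variable determined after randomisation and tied to the arm pathways, without restricting its use. If it enters an arm-effect model for an outcome pooling CHW and clinic data, the estimate is not the total intervention effect.

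The illustrated shift of -0.11 to +0.26 shows only that the distortion can matter and can take either sign. It rests on assumed clinic shares, an assumed common clinic rate, the planning values of 10% and 50%, and a linear model. It is not an estimate of what would happen in this trial. The exposure is confined to the pooled secondary outcomes, so this is a wording correction worth making and no threat to the primary comparison.

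**What to change.** In section 2.8.4, state that place of diagnosis and treatment will not be a covariate in any model that estimates an arm effect. State that it will instead be reported as an outcome, as a descriptive breakdown, or in a determinants or mediation analysis declared as exploratory.

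In the same edit, add province to the arm-effect models, since allocation was done within province. The two provinces also differ sharply in the mix of treatments given: section 2.8.2 shows malaria as 47 of 5,901 listed treatments in Kunduz (0.8%) and 2,471 of 9,818 in Nangarhar (25.2%).

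Leave the other listed covariates unchanged; the argument here does not reach symptom severity or range.

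The cost is a few sentences. Data collection, sample size and the primary comparison are not affected.

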## Laboratory Methods:

### RDT Selection:

In-line with national policy the study will use: CareStart™ 3-line Pf (HRP2) + Pan (pLDH) malaria rapid diagnostic test (AccessBio, New Jersey, USA). Recently, this test was evaluated in Afghanistan and found to have accuracy >95% and to match the WHO criteria for accuracy.

### Sample Collection:

Filter paper blood spots will be collected from participants. These will be collected using clean disposable lancets and gloves at the same time as the RDT is used. If the RDT is not used (i.e. in the non-intervention group) then the filter paper will be collected during the consultation. Filter papers will be stored in ziplock bags with silica beads. They will be returned to the clinic within 7 days and stored in a refrigerator (4^o^C) until shipped to Kabul for evaluation (see 2.8.4, below)

### RDT Accuracy:

RDT accuracy and, importantly, user interpretation of the results will be assessed under field conditions.

RDT accuracy will be determined by comparing PCR results for filter paper blood spots as the gold standard against the RDT result noted on the case-record form.

The accuracy of user interpretation will be determined by cross-checking RDT results noted by CHWs on each case record form, with RDT results recorded separately by an independent evaluator (i.e. all RDTs will be double-blind read). Because RDTs are liable to become falsely positive if exposed to humidity post-execution, CHWs will be instructed to store all RDTs in zip-lock bags with silica gel immediately after reading. The stored RDTs will be collected by field workers and undergo a second reading/interpretation by study registrars within 7 days.

### PCR Evaluation:

Filter paper blood spots will be collected in triplicate for all patients enrolled in the study and processed in Kabul. As described previously, DNA will be extracted with the crude TE buffer method[1], while the Mangold melt-curve real-time PCR[2] will be run to detect *Plasmodium* sp. DNA and discriminate between species. The assay will not be performed quantitatively. A random selection of 10% of all filter paper blood spots will be sent to the LSHTM malaria reference centre for re-evaluation by alternative PCR methods and quality control.

## Ethical Issues:

### Informed consent:

Written informed consent will be obtained from all study participants, including the community health workers. A consent form will be applied to the CHWs prior to the start of the study and they will be free to object to their inclusion in the research (annex 8).

Patients consulting with CHWs will be asked to provide informed consent following a verbal description of the risks, benefits and procedures and will be asked to sign or mark the form to indicate that they agree to take part in the study.

### Confidentiality:

Patient identities will only be known to the CHWs. The CHWs will keep a record of who the patients are, but this is only to be accessed in the case of mistreated Pf malaria (see below). On forms used for noting routine data, only the patient number will be noted, so no personal identifying information will be available to anyone.

### Risks and potential adverse events:

There are minimal risks associated with this study. Blood samples would, in most cases, be taken anyway for the application of the RDT is associated with minimal risk of secondary infection at the puncture site and with mild pain.

The main risk is in the mistreatment of falciparum malaria with either no antimalarial or with an ineffective antimalarial (i.e. CQ). Currently, falciparum malaria is quite rare in the study areas (although it may vary seasonally and geographically) so the risk of this occurrence is low. According to the National Guidelines and the study protocol, all Pf positive patients will be referred to a clinic for further evaluation which further reduces the risk of this occurring, since all clinics will have parasitological diagnosis available (either through RDT or through microscopy).

The trial intervention arm is unlikely to increase this risk, in fact, rather the opposite. This potential adverse event will be monitored throughout the trial and its occurrence will be reported to the Data Safety and Monitoring Board (DSMB). Immediately following a PCR result which is positive for Pf (regardless of coinfection), results from the patient record form will be cross checked to see which treatment was given. Because of logistical constraints, PCR results will not be known for more than 2 weeks after the initial assessment of the patient. Every effort will be made to trace the patient and ensure that they have recovered. If not, they will be referred to the health facility for further treatment.

Depending on the frequency with which this event occurs, the study staff will inform the DSMB of any action being taken which could include re-training of staff or withdrawal of CHWs from the trial. All efforts will be made to follow-up the patient within a few days of knowing the PCR result. All patients will be advised by CHWs to seek treatment at the clinic if symptoms recur or continue following the treatment.

# Programme Implementation:

## Staff structure:

The staff structure will match the current setup, although roles will be slightly changed. The staff structure is as below:

## Staff roles:

- - 1. Technical Team: The technical teams consists of the Principle Investigators, Data Coordinator, the HN-TPO Deputy Programme Manager, and Merlin’s Country Health Director. This team is responsible for all management issues related to the project.
    2. Provincial management teams are responsible for implementing the programme according to the protocol, ensuring that data is adequately recorded and entered and ensuring that all staff have adequate training. They are responsible for monitoring of progress and reporting of adverse events.
    3. Field Workers: Are each responsible for a cluster of 3-4 clinics. They are responsible for supervising the registrars and ensuring that the project is conducted per protocol, reporting of adverse events, and ensuring that data and samples are stored and transported appropriately.
    4. Registrars: The registrars (one per clinic) will each supervise between 3 and 10 CHWs and the CHS of the clinic. This will be to ensure that they are collecting informed consent from patients, recording data correctly, bringing samples and patient record to the clinic on a regular basis (once per week). Registrars are also responsible for handling referred cases and ensuring that their data is noted atthe clinic level.
    5. CHWs – Will be participants in the study, in that their decisions in diagnosis will be recorded. They will also be collecting data on the patient tracking form.

## Staff training:

Training of all provincial and clinic staff will be conducted by senior technical staff and project managers in the provinces. Registrars will be trained in the study protocol and SOPs, including ethical issues, blood safety, data recording, data processing and study monitoring.

CHWs will be trained according to the intervention arm, but all will be trained to the same standard in blood safety, enrolment characteristics, the consent process and reporting of adverse events.

**Curriculum for CHS and CHW training:**

| **Training Topic** | **Contents** | **Registrars** | **Arm 1** | **Arm 2** | **Arm 3** |
| --- | --- | --- | --- | --- | --- |
|  |  |  |  |  |  |
| *Trial Procedures* | 2 day | Trainer: Conducted by ACTc senior researchers | | | |
| Introductory training | Objectives and overview of the study – tone is not on treatment accuracy, but on different methods for diagnosis and treatment of illness at community level |  | **√** | **√** | **√** |
| Form Filling | Introduction to the form – what information is collected  Each section of the form  How to fill the form (ticking boxes)  Making corrections of mistakes  Practice using a series of case studies | **√** | **√** | **√** | **√** |
| Specimen Collection | Blood and sharps safety  Taking a blood spot  Storing the blood spot in package | **√** | **√** | **√** | **√** |
| Package training / equipment provided | Package contents  Patient numbers  Process for enrolling patients – consent forms  Handing the package to the registrar | **√** | **√** | **√** | **√** |
| Ethics and Consent | Basic Ethics – human use in research.  Consent – what is it? How to get it? | **√** | **√** | **√** | **√** |
| Fraud and bogus data collection | What happens?  How do we detect it? | **√** | **√** | **√** | **√** |
| Basic SoP for field data collection | Run through the CHW SoP for recruitment | **√** | **√** | **√** | **√** |
| Advanced Training in trial SoP | Covers all sections from Registrar and below | **√** |  |  |  |
| *Intervention Training* |  |  |  |  |  |
| *Length and Trainers* | 2 days for clinics in intervention arms | Trainers: Master trainers – from NGOs and MRC staff; [name] (HealthNet malaria master trainer, JAA) and [name] (HealthNet malaria master trainer, KDZ). Master trainers will train CHSs who will train CHWs in the intervention arm 1. | | | |
| Refresher Training of ToT |  | For Master Trainers in Arm 1 | | | |
| RDT Training* | Copied from the CBMM and any other training documents developed by NMLCP and partners |  | **√ -** possibly without RDT | **√** | - |
| RDT+ Training | Identified by ACTc team and added for phase II |  | - |  | **√** |

* Master trainers trained by NMLCP; Master trainers CHWs (in their own clinics).

## Implementation Plan:

The initial plan for implementation is described in the table below:

|  | April | | | | May | | | | June | | | | July | | | | Aug | | | | Sept | | | | Oct | | | | Nov | | | | Dec | | | |
| --- | --- | --- | --- | --- | --- | --- | --- | --- | --- | --- | --- | --- | --- | --- | --- | --- | --- | --- | --- | --- | --- | --- | --- | --- | --- | --- | --- | --- | --- | --- | --- | --- | --- | --- | --- | --- |
|  | 1 | 2 | 3 | 4 | 1 | 2 | 3 | 4 | 1 | 2 | 3 | 4 | 1 | 2 | 3 | 4 | 1 | 2 | 3 | 4 | 1 | 2 | 3 | 4 | 1 | 2 | 3 | 4 | 1 | 2 | 3 | 4 | 1 | 2 | 3 | 4 |
| **Activity** |  |  |  |  |  |  |  |  |  |  |  |  |  |  |  |  |  |  |  |  |  |  |  |  |  |  |  |  |  |  |  |  |  |  |  |  |
|  |  |  |  |  |  |  |  |  |  |  |  |  |  |  |  |  |  |  |  |  |  |  |  |  |  |  |  |  |  |  |  |  |  |  |  |  |
| **Study Preparation:** |  |  |  |  |  |  |  |  |  |  |  |  |  |  |  |  |  |  |  |  |  |  |  |  |  |  |  |  |  |  |  |  |  |  |  |  |
| Ethics Review complete (London and Kabul) |  |  |  |  |  |  |  |  |  |  |  |  |  |  |  |  |  |  |  |  |  |  |  |  |  |  |  |  |  |  |  |  |  |  |  |  |
| Purchasing of key items |  |  |  |  |  |  |  |  |  |  |  |  |  |  |  |  |  |  |  |  |  |  |  |  |  |  |  |  |  |  |  |  |  |  |  |  |
| Training of Technical Staff |  |  |  |  |  |  |  |  |  |  |  |  |  |  |  |  |  |  |  |  |  |  |  |  |  |  |  |  |  |  |  |  |  |  |  |  |
| Training of Field Staff |  |  |  |  |  |  |  |  |  |  |  |  |  |  |  |  |  |  |  |  |  |  |  |  |  |  |  |  |  |  |  |  |  |  |  |  |
| Pre-intervention Survey |  |  |  |  |  |  |  |  |  |  |  |  |  |  |  |  |  |  |  |  |  |  |  |  |  |  |  |  |  |  |  |  |  |  |  |  |
| Training of CHWs |  |  |  |  |  |  |  |  |  |  |  |  |  |  |  |  |  |  |  |  |  |  |  |  |  |  |  |  |  |  |  |  |  |  |  |  |
|  |  |  |  |  |  |  |  |  |  |  |  |  |  |  |  |  |  |  |  |  |  |  |  |  |  |  |  |  |  |  |  |  |  |  |  |  |
| **Study Implementation** |  |  |  |  |  |  |  |  |  |  |  |  |  |  |  |  |  |  |  |  |  |  |  |  |  |  |  |  |  |  |  |  |  |  |  |  |
| Enrolment of Patients (Phase 1) |  |  |  |  |  |  |  |  |  |  |  |  |  |  |  |  |  |  |  |  |  |  |  |  |  |  |  |  |  |  |  |  |  |  |  |  |
| Enrolment of Patients (Phase 2) |  |  |  |  |  |  |  |  |  |  |  |  |  |  |  |  |  |  |  |  |  |  |  |  |  |  |  |  |  |  |  |  |  |  |  |  |
| Laboratory work (PCR) |  |  |  |  |  |  |  |  |  |  |  |  |  |  |  |  |  |  |  |  |  |  |  |  |  |  |  |  |  |  |  |  |  |  |  |  |
| Laboratory work (Reference microscopy) |  |  |  |  |  |  |  |  |  |  |  |  |  |  |  |  |  |  |  |  |  |  |  |  |  |  |  |  |  |  |  |  |  |  |  |  |
|  |  |  |  |  |  |  |  |  |  |  |  |  |  |  |  |  |  |  |  |  |  |  |  |  |  |  |  |  |  |  |  |  |  |  |  |  |
| **Data Analysis and Reporting** |  |  |  |  |  |  |  |  |  |  |  |  |  |  |  |  |  |  |  |  |  |  |  |  |  |  |  |  |  |  |  |  |  |  |  |  |
| Completion of data entry |  |  |  |  |  |  |  |  |  |  |  |  |  |  |  |  |  |  |  |  |  |  |  |  |  |  |  |  |  |  |  |  |  |  |  |  |
| Interim Data analysis and Evaluation |  |  |  |  |  |  |  |  |  |  |  |  |  |  |  |  |  |  |  |  |  |  |  |  |  |  |  |  |  |  |  |  |  |  |  |  |

